### Assignment of interventions

Practices will be randomised on a 1:1 basis to the intervention and standard care groups. We will use block randomisation within each setting. In the CPRD and ResearchOne, we will stratify by region. The allocation sequence will be generated by an independent statistician who will be blinded to practice name and the allocation sequence will be concealed from the study team. Once practices have been allocated, the trial coordinator will inform practices about their allocation and distribute study materials.

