### Study population

This study is taking place in English primary care, with general practices recruited from three settings: (1) the Clinical Practice Research Datalink (CPRD),^12^ a primary care database based on Vision software and covering 8% of the UK population; (2) ResearchOne, a primary care database based on TPP SystmOne software^13^ and covering 7.6% of the UK population and (3) iPLATO text messaging software users in London.^14^

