### Sample size calculation

The sample size calculation is based on a comparison between influenza vaccine uptake in the intervention group, in which a text message influenza vaccination reminder will be sent to eligible patients, and influenza vaccine uptake in the standard care group. A cluster-level analysis of the practice-specific proportions will be undertaken and the sample size calculation estimates the number of practices required for the study. A systematic review of reminders for influenza vaccination reported that reminders (of any type) for influenza vaccine among adults increased the uptake, with an OR of 1.66, 95% CI 1.31 to 2.09).^16^ However, a text messaging vaccine reminder trial among children in the USA found only a 9% increase (RR=1.09, 95% CI 1.04 to 1.15).^9^ Therefore, we have chosen to power our study for a risk ratio of 1.075, representing an increase from 54% (uptake in the CPRD 2012/2013) to 58%.

At 90% power and 5% significance, with an ICC by general practice of 0.024 and an average of 750 eligible patients per practice, we will require 100 practices (50 per arm) to identify a 7.5% increase in vaccine uptake from 54% to 58%. To account for differences in the number of eligible patients per practice and the proportion with mobile phone numbers recorded, we have chosen to recruit and randomise 150 practices to the study.

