### Outcomes

The aims of the study are (1) to develop the methodology for conducting cluster randomised trials of text messaging interventions using routine electronic health records and (2) to implement a cluster randomised trial to test the effectiveness of using a text messaging influenza vaccine reminder in achieving an increase in influenza vaccine uptake in patients aged 18–64 with chronic conditions compared with standard care.

To address aim 2, we will examine the proportion of eligible patients who received the influenza vaccination by 31 December 2013 (primary outcome). This will be stratified by risk group, age and sex. A secondary outcome will be the proportion of eligible patients who were sent a text message to remind them about flu vaccine.

To address aim 1, we will measure the following as secondary outcomes:
Practice recruitment rate (based on the number of practices invited across three trial settings, and the number recruited);The proportion of intervention practices and standard care practices that sent a text message to eligible patients;The proportion of practices reporting any problems with delivering the message;The availability of data to examine text message receipt and vaccine uptake in each risk group;The time and cost required to gather data.

In the patient substudy, we will also examine the acceptability of text messaging to patients, by measuring the proportion of patients who reported problems with the text message.

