## Statistical methods

A cluster-level analysis will be performed using practice-specific proportions as observations. We will compare vaccine uptake in the intervention and standard care groups using a t test, with the size of clusters taken into account. A series of descriptive statistics will describe the methodological outcomes.

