### Sensitivity and subgroup analyses

Our primary analysis will be an intention to treat analysis. However, to account for any contamination between the standard care and intervention arms, we will carry out a per-protocol analysis.

Where available, we will also measure the difference in vaccine uptake, comparing practices that used the exact wording of the message in the study protocol with practices that used an alternative message. We hypothesise that practices using our message (based on behavioural theory) will have a higher uptake than an alternative designed by the practice. As this will be a non-randomised comparison, we will adjust for confounders.

Finally, we will compare the effectiveness of the text message based on the time of day that it was sent to patients. We hypothesise that messages sent in the late afternoon will have more effect than those sent at earlier times of the day, when patients may not have the time to respond.

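### The primary t test allows for cluster size but not for the setting and region strata used to randomise, so it is conservative to the extent that those strata predict uptake

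*Protocol article*

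**What the plan says.** The design is set out in the Protocol article under Assignment of interventions: "Practices will be randomised on a 1:1 basis to the intervention and standard care groups", and then "We will use block randomisation within each setting. In the CPRD and ResearchOne, we will stratify by region". Study population gives "general practices recruited from three settings": CPRD, ResearchOne and London iPLATO users. CPRD and ResearchOne are therefore each divided into region strata, while London is a single blocked stratum.

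The primary analysis is given under Statistical methods: "A cluster-level analysis will be performed using practice-specific proportions as observations". The arms are compared "using a t test, with the size of clusters taken into account". Cluster size is the only design feature mentioned; setting and region are not.

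Two other statements could be taken to fill the gap, but neither does. Under Outcomes, "This will be stratified by risk group, age and sex" describes a breakdown by patient characteristics, not by the randomisation strata. Under Sensitivity and subgroup analyses, "As this will be a non-randomised comparison, we will adjust for confounders" applies only to the comparison of message wordings.

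**The concern.** Blocking within strata makes the arms nearly equal in their mix of settings and regions. Differences in uptake between strata therefore largely cancel out of the difference between arms. A two-sample t test without the strata still counts those differences in its variance estimate, so its standard error describes simple randomisation rather than the design used.

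If uptake varies by setting or region, the confidence interval is then wider than it need be, the p-value is conservative, and some of the power that stratification could give is left unused. This matters in a trial powered for a difference of only four percentage points.

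**Working it through.** **1. Inputs from Sample size calculation.** "At 90% power and 5% significance, with an ICC by general practice of 0.024 and an average of 750 eligible patients per practice"; uptake 54% against 58%; 50 practices per arm required; 150 practices to be randomised. I take the 5% as two-sided, because the article does not say.

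**2. The plan's own figure.** Design effect = 1 + 749 × 0.024 = 18.976. Two proportions at two-sided 5% and 90% power need 3,235 patients per arm without clustering. Practices per arm = 3,235 × 18.976 / 750 = 81.85, so 82, not 50. That discrepancy is a separate matter and this point does not rest on it. Only the variance inputs are used below.

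**3. Standard error without strata.**
- Mean binomial variance = (0.54 × 0.46 + 0.58 × 0.42) / 2 = 0.2460.
- SD of a practice proportion = √(0.2460 × 18.976 / 750) = 0.0789.
- SE with 75 practices per arm = 0.0789 × √(2/75) = 0.01288.
- Share of this variance lying between practices = 0.024 / (18.976 / 750) = 95%, so strata that predict practice uptake could act on nearly all of it.

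**4. Closed form, perfect balance within strata.** Let R² be the share of the variance of practice proportions explained by the strata (assumed; not in the document).
- True SE = 0.01288 × √(1 − R²).
- Type I error = 2Φ(−1.96 / √(1 − R²)).
- Unadjusted power = Φ((0.04 − 1.96 × 0.01288) / true SE).
- Adjusted power = Φ(0.04 / true SE − 1.96).

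| R² | SE overstated by | Type I error | Power unadjusted | Power adjusted |
|---|---|---|---|---|
| 0 | 0% | 5.0% | 87.4% | 87.4% |
| 0.1 | 5% | 3.9% | 88.6% | 90.5% |
| 0.2 | 12% | 2.8% | 90.0% | 93.5% |
| 0.3 | 20% | 1.9% | 91.4% | 96.0% |

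These are upper limits on the effect, because blocks can be incomplete and stratum terms use degrees of freedom.

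**5. Simulation with incomplete blocks.** Assumptions: 15 CPRD, 75 ResearchOne and 60 London practices; 8 + 9 region strata and one London stratum; blocks of 4; practice SD 0.0789, the same for every practice; 8,000 runs under no effect and 4,000 under a four-point effect for each R². The unstratified t test is compared with a linear model containing stratum effects.

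| R² | Mean t-test SE | Actual SD of estimate | Type I, t test | Type I, adjusted | Power, t test | Power, adjusted |
|---|---|---|---|---|---|---|
| 0 | 0.01285 | 0.01280 | 4.9% | 5.1% | 86.9% | 86.0% |
| 0.05 | 0.01288 | 0.01273 | 4.9% | 5.3% | 88.6% | 88.2% |
| 0.1 | 0.01289 | 0.01246 | 4.4% | 5.3% | 88.5% | 89.4% |
| 0.2 | 0.01288 | 0.01183 | 3.0% | 5.3% | 89.0% | 92.1% |
| 0.3 | 0.01289 | 0.01105 | 2.3% | 5.3% | 90.6% | 95.2% |
| 0.5 | 0.01292 | 0.00970 | 1.1% | 4.9% | 93.3% | 99.1% |

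The SE is overstated by about 3%, 9% and 17% at R² of 0.1, 0.2 and 0.3 (0.01289/0.01246, 0.01288/0.01183, 0.01289/0.01105), less than in step 4. The change in power from adjusting is −0.9, −0.4, +0.9, +3.1 and +4.6 points at R² of 0, 0.05, 0.1, 0.2 and 0.3. In this layout adjustment starts to pay somewhere between R² of 0.05 and 0.1. Simulation error is about 0.2 points for type I error (√(0.05 × 0.95 / 8,000)) and 0.5 points for power (√(0.87 × 0.13 / 4,000)).

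**The case against.** The strongest objection is that the article is condensed. It does not call the t test unadjusted, a stratified t test is also a t test, and the full protocol or analysis plan may list the strata. That is fair as a caution, and a reader should not infer that the investigators have decided against adjustment. It does not remove the point: the article names the test and names the one design feature it allows for, and that description does not match the allocation stated a few sections earlier.

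The second objection is that the harm is conditional. This stands in full. Nothing in the document says how much of the variation in uptake lies between settings or regions. If the answer is none, the t test is correct (type I error 4.9%) and adjusting costs about one point of power.

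The third is that sparse strata weaken the effect. This also stands. Only 40 eligible CPRD practices are to be invited (Recruitment), so some region blocks may be incomplete. The less well the strata balance, the closer the unstratified standard error is to the truth. That is why the simulated effects, rather than the closed-form ones, are the ones to rely on.

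**Conclusion.** The stated primary test does not reflect the stated randomisation. To the extent that setting and region predict uptake, its standard error is too large and its p-value conservative. For assumed R² of 0.1 to 0.3 the simulated type I error is 4.4% to 2.3%, and adjusting would add about 1 to 5 points of power with 150 practices. At R² of 0 there is no distortion. The type I error figures depend on R² and the assumed strata layout; the power figures also depend on the ICC and uptake in the article. The simulation does not model unequal practice sizes.

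Three stronger readings are not supported:
- **That the result would be invalid or prone to false positives.** The t test did not exceed 5% in any scenario tried.
- **That the benefit of stratifying is lost altogether.** Unadjusted power rises from 86.9% to 90.6% as R² goes from 0 to 0.3, because the estimate itself becomes more precise.
- **That this omission leaves the trial short of its 90% power.** At R² of 0 the stated inputs give about 87% with 150 practices whichever test is used. That shortfall comes from the sample size calculation.

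This is a moderate point about efficiency, worth correcting because the correction costs little.

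**What to change.** Under Statistical methods, replace the unstratified t test with a practice-level linear regression of the practice proportion on arm, setting, and region within CPRD and ResearchOne (London as one category). A t test stratified in the same way would also do. Keep the allowance for cluster size that the plan already states. Add a rule for pooling sparse regions and fix it before unblinding; this needs only the number of practices per region, not their allocation or outcomes. If the full protocol or analysis plan already specifies this, the article's description should be brought into line with it.

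The change affects analysis wording only and needs no new data. It costs one degree of freedom per stratum less one. The number of regions is not stated; the 18 strata assumed above would use 17, and 15 to 20 of about 148 is a reasonable expectation before pooling. If the strata turn out not to predict uptake, the price is about one point of power.

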### Blinding

Practices in this study will be randomised to intervention or standard care groups, but general practice staff will not be blinded. However, academic investigators and trial statisticians will manage and review data without knowledge of the allocation.

### Interventions

Practices will be allocated to an intervention or standard care arm. Those in the intervention arm will be asked to send an influenza vaccination text message reminder to their under 65 at-risk patients. This includes patients who are under 65 with chronic heart disease, chronic neurological disease, diabetes, chronic kidney disease, chronic liver disease, chronic respiratory disease and immunosuppression, as set out by the Chief Medical Officer.^17^ Most practices will identify eligible patients based on their electronic medical records using their established systems. Practices use a standard set of Read codes (available from Primis^18^) to determine patient eligibility for influenza vaccination.

The message content that practices will be asked to send is shown in box 1. This single text message was designed to be a pragmatic, uncomplicated intervention that would not discourage practices from participating, but that aims to address some of the key barriers to vaccination.^3^ It was specifically designed to target more than one factor influencing behaviour: first, the text message represents a recommendation from the general practitioner (GP); second, it indicates the severity of flu and that the patient is susceptible to flu; third, it acts as a prompt to patients who might have simply forgotten to make an appointment.
Box 1 Recommended text message content in the trial intervention arm.Hello *PATIENT NAME*, to reduce your risk of serious health problems from flu, we recommend vaccination. Call *PRACTICE PHONE NUMBER* to book. *PRACTICE NAME.*

Practices in the intervention group will receive guidance notes regarding delivery of the message (content, timing, eligible patients) and an incentive payment of £200. Practices will be instructed to continue with any other aspect of their seasonal flu campaign as planned, in addition to the text message. An online questionnaire will be sent to practices in the intervention arm to ascertain feedback from practice staff about delivery of the intervention.

Practices allocated to the standard care group will be asked to continue with their seasonal flu campaign as planned.

#### Substudy for patient feedback

A substudy will be conducted in two participating intervention practices. Each practice will send an anonymous questionnaire to patients who were targeted with the text message reminder. This questionnaire will address patient acceptability of the text message.

### Outcomes

The aims of the study are (1) to develop the methodology for conducting cluster randomised trials of text messaging interventions using routine electronic health records and (2) to implement a cluster randomised trial to test the effectiveness of using a text messaging influenza vaccine reminder in achieving an increase in influenza vaccine uptake in patients aged 18–64 with chronic conditions compared with standard care.

To address aim 2, we will examine the proportion of eligible patients who received the influenza vaccination by 31 December 2013 (primary outcome). This will be stratified by risk group, age and sex. A secondary outcome will be the proportion of eligible patients who were sent a text message to remind them about flu vaccine.

To address aim 1, we will measure the following as secondary outcomes:
Practice recruitment rate (based on the number of practices invited across three trial settings, and the number recruited);The proportion of intervention practices and standard care practices that sent a text message to eligible patients;The proportion of practices reporting any problems with delivering the message;The availability of data to examine text message receipt and vaccine uptake in each risk group;The time and cost required to gather data.

In the patient substudy, we will also examine the acceptability of text messaging to patients, by measuring the proportion of patients who reported problems with the text message.

## Data collection methods

All patient-level outcomes will be evaluated through analysis of routinely collected data. In practices that contribute data to the CPRD or ResearchOne, relevant data will be extracted from the database using specified Read codes. Within London practices using iPLATO software, data will be extracted by the clinical software supplier of the practice or the practices themselves.

We will extract data on age, sex, clinical risk group (based on historical data from the medical record and prescription data), vaccination reminder type (text, letter, phone call, face to face), vaccination uptake, death, transfer out of practice, flu and flu-like illness, and hospital admissions. Uptake and patient outcomes will be analysed from 1 September to 31 December 2013. All of these data items are routinely collected by general practices and stored in their electronic health record, and follow-up for practices will be complete using this method. Time and cost of data collection using these methods will be estimated. All data will be stripped of personal identifiers before being supplied to the study team, and will be stored securely as defined in the protocol.

We will record the number of practices approached, recruited and analysed. An online questionnaire, emailed to each practice in the intervention group, will ascertain practice acceptability of the intervention. The postal questionnaire to patients in the substudy will estimate patient acceptability.

## Statistical methods

A cluster-level analysis will be performed using practice-specific proportions as observations. We will compare vaccine uptake in the intervention and standard care groups using a t test, with the size of clusters taken into account. A series of descriptive statistics will describe the methodological outcomes.

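### The primary t test on practice proportions makes no use of each practice's 2012/13 uptake, so it gives up precision that the planned sample may need

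*Protocol article*

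**What the plan says.** Under Statistical methods the unit of analysis is the practice: "A cluster-level analysis will be performed using practice-specific proportions as observations". The primary test follows: "We will compare vaccine uptake in the intervention and standard care groups using a t test, with the size of clusters taken into account". Cluster size is the only feature of a practice that enters.

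Earlier uptake is not used elsewhere in the design:
- Assignment of interventions blocks within setting and stratifies by region in CPRD and ResearchOne.
- Data collection methods confines the uptake analysis to 1 September to 31 December 2013.
- Sensitivity and subgroup analyses mentions adjustment only for the non-randomised comparison of message wordings.

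Three statements bear on whether a baseline could be had:
- The planning effect is described as "representing an increase from 54% (uptake in the CPRD 2012/2013) to 58" per cent, so 2012/13 uptake has been read from at least one of the three data sources.
- Of the extracted items, which include vaccination uptake, Data collection methods says: "All of these data items are routinely collected by general practices and stored in their electronic health record".
- Inclusion criteria excludes practices that texted flu reminders in the 2012/2013 season.

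**The concern.** In a practice-level analysis the noise is the spread of practice proportions. With several hundred patients per practice, little of that spread is patient sampling; most of it is that practices differ. Practices with high uptake one year may well have high uptake the next. If so, last season's uptake would absorb part of the spread and narrow the interval around the treatment effect. It would also take out of the estimate any chance imbalance in prior uptake, which stratifying by region does not directly control.

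At stake is the width of the confidence interval and the chance of detecting a 4-point difference. This matters more here because the unadjusted analysis falls somewhat short of the stated 90% power even with all 150 practices.

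**Working it through.** **Inputs, all from Sample size calculation:** uptake 54% against 58% ("we have chosen to power our study for a risk ratio of 1.075"); "At 90% power and 5% significance"; "with an ICC by general practice of 0.024"; "an average of 750 eligible patients per practice"; 100 practices calculated, 150 to be randomised. Sidedness is not stated, so two-sided is assumed. The correlation r between a practice's 2012 and 2013 uptake is not given, so a range is shown.

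**1. The plan's own figure.** The design effect is 1 + 749 × 0.024 = 18.976. The standard two-proportion formula gives 3,235 patients per arm, so 3,235 × 18.976 / 750 = 81.8, or 82 practices per arm. The stated 50 per arm does not reproduce. That is a separate matter; here it only sets the unadjusted starting point.

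**2. Spread of a practice proportion.** The mean binomial variance is (0.54 × 0.46 + 0.58 × 0.42) / 2 = 0.246.
- SD = √(0.246 × 18.976 / 750) = 0.0789, or 7.9 points.
- Between-practice share = 0.024 / (0.024 + 0.976/750) = 0.0240 / 0.0253 = 94.9%.
- The share varies with practice size: 83% at 200 patients, 91% at 400, 96% at 1,000.

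**3. Unadjusted precision with 75 per arm.** SE = 0.0789 × √(2/75) = 0.0129, or 1.29 points. The noncentrality is 4 / 1.29 = 3.10, and the two-sided t test has power of about 87%.

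**4. Adjusted precision.** Regressing 2013 uptake on arm and 2012 uptake multiplies the SE by √(1 − r²) and costs one degree of freedom (147 instead of 148). Practices needed per arm for 90% power become about 81.8 × (1 − r²), rounded up. Power below is from the noncentral t distribution for a 4-point difference.

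| Assumed r | SE multiplier | SE, points (75 per arm) | Power (75 per arm) | Needed per arm for 90% (normal approx.) |
|---|---|---|---|---|
| 0 (t test) | 1.00 | 1.29 | 87% | 82 |
| 0.2 | 0.98 | 1.26 | 88% | 79 |
| 0.3 | 0.95 | 1.23 | 90% | 75 |
| 0.5 | 0.87 | 1.12 | 95% | 62 |
| 0.6 | 0.80 | 1.03 | 97% | 53 |
| 0.7 | 0.71 | 0.92 | 99% | 42 |

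With 75 per arm, 90% power is reached from r of about 0.3. With only 50 per arm it would need r of about 0.62. None of these figures allows for unequal practice sizes.

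**The case against.** The strongest reply is that nothing here is an error. The t test is valid under randomisation, its confidence interval already covers chance imbalance, and blocking by setting with regional strata limits some imbalance. That stands: this is a point about efficiency, and a reader who infers bias in the primary analysis would be wrong.

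Three other inferences are tempting and not supported.
- **That the 95% is stable, and hence the expected gain.** A single ICC separates between-practice from within-practice variance in one season. It cannot tell lasting differences from those of one year, such as supply, staffing or that year's campaign. Even r = 0.7 means that last season explains 49% of the variance.
- **That the protocol already collects the baseline.** The historical data in Data collection methods serve to classify clinical risk group. Prior uptake is not listed for extraction. Availability is shown only for CPRD, and there as an aggregate rate. For ResearchOne and the London practices, where suppliers or the practices themselves extract the data, it is a reasonable inference and no more.
- **That adjustment will restore the power.** It does so only if r is about 0.3 or more. At r = 0.2 the gain is about one percentage point of power.

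It can also be said that covariates are commonly left to an analysis plan, which is not shown. That carries some weight, since such a plan could add an adjusted analysis. But the article names the primary test itself, and that choice can be questioned as it stands.

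**Conclusion.** The point holds as a recommendation on precision. The primary test omits a pre-intervention measure of the same outcome, taken in a season for which practices that texted flu reminders are excluded. The starting position is about 87% power with 150 practices. The improvement ranges from negligible at r = 0.2 to a 29% smaller SE and about 99% power at r = 0.7.

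That the covariate is absent is certain from the text. The size of the gain is not: it rests on an assumed r, two-sided testing, equal practice sizes and the protocol's own ICC. The downside in the analysis is small, because even an uninformative baseline costs only one degree of freedom.

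**What to change.** Add to the extraction request each practice's uptake from 1 September to 31 December 2012, with the same codes, age range and risk-group definition as for 2013. Before unblinding, prespecify as primary a practice-level linear regression of 2013 uptake on arm and 2012 uptake, reporting the adjusted difference with its 95% confidence interval. Carry over the allowance for cluster size that the t test was to have, so that the change adds a covariate without dropping that feature. Keep the unadjusted t test as a sensitivity analysis.

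The costs are a somewhat larger extraction, the retrospective reconstruction of who was eligible in 2012, and possibly missing baselines in some practices. Missing baselines can be handled by mean imputation or a missing indicator, chosen in advance, so that every randomised practice stays in the analysis. No additional practices or patient contact are needed.

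### The primary t test makes no use of age, sex and risk-group data already planned for extraction; the test is valid, but it gives up precision that a two-stage cluster-level analysis could recover cheaply

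*Protocol article*

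**What the plan says.** Under Statistical methods, the unit of analysis is the practice: "A cluster-level analysis will be performed using practice-specific proportions as observations". The test follows: "We will compare vaccine uptake in the intervention and standard care groups using a t test, with the size of clusters taken into account". No covariate is named for it.

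Under Data collection methods, patient characteristics are to be taken from routine records: "We will extract data on age, sex, clinical risk group (based on historical data from the medical record and prescription data". Under Outcomes, directly after the primary outcome is defined, the article adds: "This will be stratified by risk group, age and sex". It does not say whether that means separate results by subgroup or a stratified comparison of the arms. The same section lists as a secondary outcome: "The availability of data to examine text message receipt and vaccine uptake in each risk group".

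Adjustment is mentioned once, under Sensitivity and subgroup analyses, for the comparison of message wordings: "As this will be a non-randomised comparison, we will adjust for confounders". Under Assignment of interventions, randomisation is blocked within setting and stratified by region in two of the three settings. Case mix is not balanced by design.

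**The concern.** Practices differ in uptake partly because their eligible patients differ in age, sex and condition. A t test on unadjusted proportions leaves that part of the variation in the error term. Clusters are large here, so almost all the uncertainty comes from variation between practices and very little from the number of patients within each. Explaining some of the between-practice variation is therefore the main way to gain precision without recruiting more practices. The target difference is 4 percentage points against a between-practice SD of about 7.7 points. At stake is some power and some width of the confidence interval, using variables that the trial already intends to collect.

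**Working it through.** **Inputs from the article (Sample size calculation):** uptake 54% against 58%; "At 90% power and 5% significance, with an ICC by general practice of 0.024 and an average of 750 eligible patients per practice"; 50 practices per arm required; 150 to be randomised, which is 75 per arm at 1:1. Sidedness is not stated, so two-sided 5% is assumed. Clusters are taken as equal at 750.

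**Input not in the documents:** R², the share of between-practice variance explained by age, sex and risk group. It is shown as a range.

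**The plan's own figure.** The individually randomised size at 90% power is 3,235 per arm. The design effect is 1 + 749 × 0.024 = 18.976. Practices per arm = 3,235 × 18.976 / 750 = 81.8, so 82 per arm (164 in all). The stated 50 per arm does not reproduce. That is a separate matter. It is relevant here only because the unadjusted test then has less than the stated 90% power even with 150 practices.

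**Where the variance lies.** The variance of a practice proportion is p(1−p) × [ICC + (1−ICC)/750]. The bracket is 0.024 + 0.976/750 = 0.024 + 0.00130 = 0.02530. The between-practice share is 0.024 / 0.02530 = 94.9%. At p = 0.56 the between-practice SD is √(0.024 × 0.56 × 0.44) = 0.0769, or 7.7 points.

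**Power with adjustment.** The bracket becomes 0.024 × (1−R²) + 0.00130. The sum of p(1−p) over the arms is 0.2484 + 0.2436 = 0.492. The SE of the difference is √(0.492 × bracket / 75), and power comes from the noncentral t with 148 degrees of freedom and noncentrality 0.04 / SE.

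| Assumed R² | Bracket | SE | Power | Equivalent extra practices |
|---|---|---|---|---|
| 0 (unadjusted) | 0.02530 | 0.01288 | 87.0% | – |
| 2% | 0.02482 | 0.01276 | 87.6% | about 3 |
| 5% | 0.02410 | 0.01257 | 88.5% | about 7 |
| 10% | 0.02290 | 0.01226 | 90.0% | about 16 |
| 20% | 0.02050 | 0.01160 | 92.9% | about 35 |

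The last column is 150 × (unadjusted bracket / adjusted bracket − 1). At 20%, for example, it is 150 × (0.02530/0.02050 − 1) = 35.

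**Chance imbalance in case mix.** The SD of the between-arm difference in uptake that is due to case mix is √(2/75) × √R² × 7.7 points. This is 0.40 points at R² = 10% and 0.56 points at 20%, against the 4-point target. It is a component of the SE shown for the unadjusted test and does not come on top of it.

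**The case against.** The strongest objection is that covariate adjustment is usually settled in the full protocol or analysis plan, neither of which is shown, and that a condensed article which names no covariates has stated nothing wrong. Silence alone would indeed be no finding. But the article is not silent on method. It names a particular test, on practice proportions, with cluster size as the only feature taken into account, and it mentions adjustment only where the comparison is not randomised. That is a stated choice, and a more precise one is available within the same cluster-level design.

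Three stronger readings are tempting and are not supported:

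- **That the unadjusted test is biased, or lets imbalance pass as an effect.** Randomisation makes the test valid, and chance differences in case mix are already part of the standard error. Only precision is lost.
- **That the characteristics serve only for subgroup tables.** The article does not say so. The stratification sentence may mean a stratified comparison. If it does, its link to the t test still has to be stated.
- **That complete covariates are assured for every patient.** Extraction is planned, but availability of data by risk group is itself an outcome. In London the data come from the software supplier or from the practices themselves.

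It is also fair to object that the gain rests on an assumed R². All eligible patients are aged 18–64 with a chronic condition, which may narrow differences in case mix, and the gain would overlap with that from adjusting for earlier-season uptake. Both points stand and limit the size. Finally, setting and region, the factors used in randomisation, are not named in the test either. Case-mix adjustment does not resolve that.

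**Conclusion.** The point holds as a modest improvement in precision. The stated primary analysis is valid and matches the basis of the sample size calculation, but it makes no stated use of patient characteristics that the trial plans to extract and links to its primary outcome. At 75 practices per arm, unadjusted power is 87.0%. It rises by 0.6 points if case mix explains 2% of between-practice variance, 1.5 points at 5%, 3.0 points at 10% and 5.9 points at 20%. These figures assume equal clusters of 750, ICC 0.024, a two-sided 5% test and an R² that the documents do not give. At the low end the gain is slight, and it would be smaller after adjustment for earlier-season uptake.

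**What to change.** Prespecify a two-stage cluster-level primary analysis.

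1. Fit a patient-level logistic regression of vaccination on age band, sex and risk-group indicators, with no arm term. Define risk group from records made before randomisation and let the indicators overlap, because a patient may belong to several groups. Average the fitted probabilities to give each practice its expected proportion.
2. Apply the planned comparison to the practice residuals (observed minus expected proportion), with cluster size taken into account as now intended.

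State in advance that stage 1 uses age and sex alone if risk group is not available at patient level for all practices, so that no practice leaves the primary analysis. Keep the unadjusted t test as a supportive analysis. Say what the stratification by risk group, age and sex under Outcomes means and how it relates to the primary test.

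The cost is one extra regression, the fallback rule and a few lines of text. No new data items and no further practices are needed. Fixing this in advance also rules out a later choice between adjusted and unadjusted results.
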